### Outcomes {12}

#### Primary endpoint

The primary endpoint will be the incidence of moderate-to-severe hypoxaemia (PaO_2_/FiO_2_ < 200, according to the Berlin definition [5]) in severe trauma patients (ISS > 15) during the first 7 ICU days. The PaO_2_/FiO_2_ ratio will be computed at least once daily (8:00 a.m.) together with the supine chest X-ray and the worst daily PaO_2_/FiO_2_ value will be taken into account to define hypoxaemia severity. In ARDS patients, the severity of hypoxaemia allows for its classification according to the Berlin definition and is strongly associated with mortality, length of recovery and quality of life [6, 7].

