### Sample size {14}

The sample size was determined to be 250 subjects per arm (i.e. 500 subjects in total). Dornase alfa is expected to reduce the incidence of moderate-to-severe hypoxaemia from 0.45 to 0.30. Considering a reasonable standard deviation of 0.03, and using Bayesian techniques [52], 200 subjects per arm were estimated to show a difference of more than 0.12 (instead of the expected 0.15). Assuming 25% loss to follow-up, this number was increased to 250 subjects per arm, although these subjects will not be replaced.

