The aim of this study is to show that the frequency of moderate-to-severe hypoxaemia is lower in the dornase alpha group than in the placebo group. The main variable is then dichotomous “moderate-to-severe hypoxaemia yes/no”, modelled in a logistic mixed regression. We will assume that this variable is Bernoulli distributed with parameter π. The logit of this parameter (linear predictor) is additively written as:
$$ \mathrm{logit}\left({\pi}_i\right)={\alpha}_0+{\alpha}_1I\left({g}_i=1\right)+{\beta}_i, $$

where:
*α*_0_ is a grand mean, with mean 0 normal prior (the variance in this normal is 6, corresponding to a low informative prior)*I*(*g*_*i*_ = 1) is a dummy covariate coded for the group of subject *i* (1 for the dornase alpha group and 0 for the placebo group) — the prior on the parameter of this covariate is the same normal as that for the grand mean*β*_*i*_ is a (random) subject effect, on which is assumed a normal prior with mean 0 and low variance (e.g. 10)

Because the linear predictor is on the logit scale, the probability for moderate-to-severe hypoxaemia will be obtained by monitoring the back-transformation of the logit.

This regression model without covariates except group will be completed for taking into account potential confounding variables. In the model, the entire set of these variables will be added and, secondly, selected using stochastic search variable selection (SSVS) [53]. In such a model, the prior distribution on each parameter is a mixture of two mean 0 normal distributions, one with low variance and the other with high variance: if the posterior weight on this second normal is strongly around 0, then the prior on the parameter is essentially driven by a normal distribution whose mean is centred on 0; this is the clue for a “non-significant” parameter.

The secondary analyses will be conducted as the main analysis with a regressive model, testing the difference of a parameter between the two groups. Only the likelihood model will be changed to take into account the type of variable studied: γ distribution for continuous variables such as length of stay and duration of ventilation. Dichotomous variables such as 30-day mortality will be studied with logistic regression.

No statistical procedure for replacing missing values will be used. All variables and subjects will be considered in the descriptive analyses, but, for inference, 20% missing data or more will result in rejection of the variable or individual.

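### The primary logistic model gives each patient a random effect that a single yes/no outcome cannot inform, so the size of the treatment coefficient, and possibly of the reported risks, depends on an arbitrary prior variance

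*Protocol article*

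**What the plan says.** The Primary endpoint section sets an incidence over the first 7 ICU days: "The primary endpoint will be the incidence of moderate-to-severe hypoxaemia". The daily PaO2/FiO2 values feed into one yes/no per patient.

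In Statistical methods for primary and secondary outcomes {20a}, that yes/no variable is "modelled in a logistic mixed regression", with "We will assume that this variable is Bernoulli distributed with parameter π". The linear predictor is logit(π_i) = α0 + α1·I(g_i = 1) + β_i. The only index is the patient; there is no day or centre index.

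The priors are:
- α0: normal with mean 0, where "the variance in this normal is 6, corresponding to a low informative prior".
- α1: "the prior on the parameter of this covariate is the same normal as that for the grand mean".
- β_i: it "is a (random) subject effect, on which is assumed a normal prior with mean 0 and low variance (e.g. 10".

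On reporting, the section says that "the probability for moderate-to-severe hypoxaemia will be obtained by monitoring the back-transformation of the logit". It does not say whether β_i is set to zero, kept for each patient, or averaged out.

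The design assumption is in Sample size {14}: "Dornase alfa is expected to reduce the incidence of moderate-to-severe hypoxaemia from 0.45 to 0.30". That section takes 200 patients per arm as enough to show a difference above 0.12.

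**The concern.** A patient-level random intercept needs repeated observations per patient. With one binary value each, the likelihood depends on β_i only through the arm-level probability averaged over it. Any variance fits equally well once α0 and α1 are rescaled. The prior variance therefore acts as a scaling constant for α1 that the data cannot check, and the text gives it only as an example.

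The value is also mislabelled. A variance of 10 is called low, yet it is larger than the 6 that the same section calls low informative for the fixed effects.

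The objective is stated in absolute incidence. If the reported probabilities come from α0 and α0 + α1 alone, they are risks for a patient with β_i = 0, not the incidences in the two arms. The gap between them would be wider than the gap in the data.

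**Working it through.** **Inputs.** Risks 0.45 and 0.30 and 200 evaluable patients per arm (Sample size {14}); N(0, 6) priors on α0 and α1 and variance 10 for β_i (Statistical methods {20a}). Assumptions of this check: other variances v for comparison, and an observed 45% against 35% as an example of a result short of the target.

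**Step 1: does the data inform the variance?** The likelihood sees only the averaged risk p_g = E[expit(α0 + α1·g + β)], with β ~ N(0, v). For each v, solve for α0 and α1 so that p_0 = 0.45 and p_1 = 0.30. With 200 per arm the maximised log-likelihood is −259.80 for v = 0, 1, 5, 10 and 20 alike. The data cannot distinguish between these values.

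**Step 2: what does the variance do to α1?** For v = 10 the solution is α0 = −0.455 and α0 + α1 = −1.898. So α1 = −1.443 and exp(α1) = 0.236. Without β_i, the odds ratio is (0.30/0.70)/(0.45/0.55) = 0.524. The same calculation for other values, with the risks at β = 0 being expit(α0) and expit(α0 + α1):

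| Variance of β_i | Implied odds ratio | Risks at β = 0 | Difference |
|---|---|---|---|
| 0 | 0.524 | 0.450 / 0.300 | 0.150 |
| 1 | 0.460 | 0.440 / 0.265 | 0.174 |
| 10 | 0.236 | 0.388 / 0.130 | 0.258 |
| 20 | 0.147 | 0.353 / 0.074 | 0.279 |

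Every row has the same averaged risks, 0.45 and 0.30.

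**Step 3: is 10 low?** The standard deviation is √10 = 3.16 on the logit scale. The central 95% range of one placebo patient's risk is expit(−0.455 ± 1.96 × 3.16), that is 0.001 to 0.997.

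**Step 4: posterior with the stated priors.** Grid posterior for (α0, α1), 200 per arm:

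| Observed | Model and reporting | Mean difference | P(difference > 0.12) |
|---|---|---|---|
| 45% vs 30% | no β_i | 0.149 | 0.73 |
| 45% vs 30% | variance 10, risks at β = 0 | 0.249 | 0.94 |
| 45% vs 30% | variance 10, averaged over β | 0.145 | 0.71 |
| 45% vs 35% | no β_i | 0.099 | 0.34 |
| 45% vs 35% | variance 10, risks at β = 0 | 0.183 | 0.76 |

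For 45% vs 30%, the posterior mean risks at β = 0 are 0.387 and 0.138, and the averaged risks are 0.448 and 0.303. The posterior median odds ratio is 0.52 (95% credible interval 0.35 to 0.78) without β_i and 0.24 (0.10 to 0.60) at variance 10. P(α1 < 0) is 0.999 in both models.

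**The case against.** The strongest reply concerns the risks. The article defines the linear predictor with β_i in it and then back-transforms the logit. Read literally, that monitors π_i for each patient, and averaging π_i within arm brings the difference back to 14.5 points. This stands: the inflation to 25–26 points is conditional, and the text supports neither reading over the other.

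Second, the stated aim is to show a lower frequency with dornase alfa, and P(α1 < 0) does not move. This also stands. A reader might infer that the trial's headline result must be wrong or that a false claim of benefit would follow; the documents do not support that.

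Third, the article never promises an odds ratio. True, but α1 is the only treatment parameter in the model, and its size is set by the chosen constant however it is reported.

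Fourth, a reader might infer that the whole model is unidentifiable. It is not: with the variance fixed by the prior, the posterior for α0 and α1 is proper. What cannot be learned is the variance of β_i.

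Fifth, the value is an example, and sensitivity analyses with three priors are planned. These are a non-informative, an optimist and a pessimist prior, and the article does not say that they cover the variance of β_i. If 10 was meant as a precision (variance 0.1), the effect would be nearly harmless: odds ratio 0.516, difference 15.3 points. The text says variance, so it would still need correcting.

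**Conclusion.** The primary model is wrongly specified as written. It contains a patient effect with no replication, whose variance the data cannot inform and which is called low although it exceeds the variance called low informative beside it. The dependence of α1 on that constant is certain: the implied odds ratio goes from 0.52 to 0.24 on the same 45% and 30%.

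The distortion of the risks, and of the probability of exceeding 0.12, arises only if probabilities are taken at β_i = 0; the article should exclude that reading. The 0.12 appears in the sample size section as the difference the trial should be able to show and is not stated as a decision rule, so its use here illustrates the size of the problem.

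The section says that secondary analyses follow the main analysis with only the likelihood changed, so the same term may carry over to other single binary outcomes. This is an inference: 30-day mortality is described there simply as logistic regression. The figures rest on the design risks, 200 evaluable patients per arm and the stated N(0, 6) priors.

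**What to change.** Remove β_i from the primary model, and from any other model with one binary outcome per patient that follows it. Keep a subject effect only where a patient contributes repeated daily measures, such as static compliance.

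State that the reported quantities are the marginal risk in each arm and their difference, obtained at each posterior draw by averaging predicted probabilities over all patients under each arm in turn. In the model without covariates this is simply expit(α0) and expit(α0 + α1). Once covariates are added, the averaging matters.

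Optionally, and as a separate improvement, put in its place terms that do have replication: the stratification factors centre and severe traumatic brain injury.

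The cost is a wording change and a small change to the model code. It needs no new data and has no effect on patients or timeline.

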### Objectives {7}

#### Primary objective

The primary objective of the TRAUMADORNASE study is to demonstrate a reduction in the incidence of moderate-to-severe hypoxaemia from 45% to 30% in severe trauma patients during the first 7 ICU days by providing aerosolized dornase alfa once during the first 2 ICU days as compared to equivalent provision of placebo (NaCl 0.9%).

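### The plan's only route to a probability is back-transforming the logit, with no averaging over patients; read at fixed values, this does not give the arm incidences of the 45% to 30% objective

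*Protocol article*

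**What the plan says.** The primary objective reads: "demonstrate a reduction in the incidence of moderate-to-severe hypoxaemia from 45% to 30% in severe trauma patients during the first 7 ICU days". The outcomes section agrees: "The primary endpoint will be the incidence of moderate-to-severe hypoxaemia". The sample size section plans on the same scale: "Dornase alfa is expected to reduce the incidence of moderate-to-severe hypoxaemia from 0.45 to 0.30", with 200 subjects per arm to show a difference of more than 0.12.

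The statistical methods section {20a} models the yes/no outcome by a mixed logistic regression whose linear predictor, for subject i, is a grand mean, a group term and a subject term. The last of these "is a (random) subject effect, on which is assumed a normal prior with mean 0 and low variance (e.g. 10"). It then gives one rule for returning to the probability scale: "the probability for moderate-to-severe hypoxaemia will be obtained by monitoring the back-transformation of the logit".

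The next paragraph extends the model: "This regression model without covariates except group will be completed for taking into account potential confounding variables". It adds: "In the model, the entire set of these variables will be added and, secondly, selected using stochastic search variable selection (SSVS"). No further read-out rule follows. The section names no covariate list, coding, centring or reference patient.

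**The concern.** The trial's question is put as two absolute incidences and the gap between them. An incidence in an arm is the average of its patients' risks. The inverse logit of a predictor evaluated at one set of values is the risk of a patient with those values. The two agree when the predictor holds nothing but intercept and group, and generally differ once it holds anything that varies between patients.

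The protocol's models contain such terms twice over: the subject effect in the base model, and the confounders in the extended model. If the reported probabilities are read at fixed values, they and their difference answer a different question from the objective. They also depend on the variance given to the subject effect or on how covariates are coded, and they cannot be set beside the planning figures or compared between models.

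**Working it through.** **Inputs from the protocol.** Arm incidences 0.45 (placebo) and 0.30 (dornase alfa), from the primary objective and the sample size section. Subject effect normal with mean 0 and example variance 10, so SD = √10 = 3.16, from section {20a}.

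**Inputs assumed, because the protocol gives none.** A covariate score, normal with mean 0 and SD 0.5, 1.0 or 1.5 on the logit scale; alternatively, one binary covariate with prevalence 30% or 50% and odds ratio 3 or 5.

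**Step 1: intercept and group only.** logit(0.45) = −0.201 and logit(0.30) = −0.847. Back-transforming these returns 0.45 and 0.30 exactly, a difference of 15.0 points. Nothing is wrong in this case.

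**Step 2: the base model as written, with the subject effect.** The arm incidence is the average of expit(μ + s·u) over a standard normal u, where μ is the arm's fixed part and s = 3.16. Solve for μ so that this average equals the stated incidence, then read expit(μ), which is the back-transformation at subject effect zero:

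- incidence 0.45 requires μ = −0.455, and expit(−0.455) = 0.388
- incidence 0.30 requires μ = −1.898, and expit(−1.898) = 0.130
- difference read: 0.388 − 0.130 = 0.258, against a true 0.150

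**Step 3: the extended model, if the same rule is carried over and read at mean covariates** (no subject effect, same equation with s the SD of the covariate score):

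| SD of score | placebo | dornase alfa | difference read |
|---|---|---|---|
| 0.5 | 0.447 | 0.290 | 15.7 points |
| 1.0 | 0.440 | 0.265 | 17.4 points |
| 1.5 | 0.430 | 0.234 | 19.6 points |

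**Step 4: the extended model read at a reference level.** For a binary covariate with prevalence q and odds ratio OR, solve (1 − q)·expit(m) + q·expit(m + ln OR) = incidence for m in each arm, and read expit(m):

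- q = 0.3, OR 3: 0.370 and 0.228, difference 14.2 points
- q = 0.5, OR 3: 0.317 and 0.189, difference 12.9 points
- q = 0.5, OR 5: 0.261 and 0.144, difference 11.8 points (unrounded risks 0.2612 and 0.1437)

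Reading at the mean therefore overstates the difference in these cases, and reading at the low-risk level understates it. The direction of effect is preserved throughout. Averaging the predicted risks returns 0.45 and 0.30 in every case, by construction.

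**The case against.** The strongest reply is that the protocol does not say what a critic might attribute to it. Four parts of that reply deserve an answer.

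- **Which model the rule belongs to.** The read-out sentence closes the description of the model with group and subject effect; the covariates come in the next paragraph. A reader might infer that the protocol plans to report a reference patient's risk from the adjusted model. It does not say so, and does not say whether a probability is read from that model at all. This stands, and it is why the covariate part is stated conditionally.
- **What is monitored.** The logit is written on a probability indexed by subject. Monitoring those individual probabilities and averaging them by arm is not excluded, and would give an incidence. This also stands: the step is unstated, not contradicted.
- **Whether it is a matter for the analysis plan.** Coding, centring and risk-scale summaries are often left there. But the protocol was not silent: it published a specific read-out, and that read-out is incomplete for the model it is attached to.
- **Size and consequence.** No rule in the protocol compares an adjusted risk difference with 0.15 or 0.12; those are planning values, and the stated aim is that the frequency is lower with treatment. The covariate figures rest wholly on assumed SDs and coding. More extreme figures can be produced: with an uncentred score of SD 1.0 or 1.5 whose zero lies 2 SD on the low-risk side, the difference read falls to 4.9 or 2.1 points. Nothing in the protocol says that covariates will be entered or read in that way, so these figures are no measure of the likely error.

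The base-model figure is not open to the last objection, since the variance of 10 is the protocol's own, though given as an example.

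**Conclusion.** The point holds as a gap in the stated read-out. The only rule for reaching the probability scale omits averaging over patients, while the objective is about averages over patients.

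In the model the rule describes, with the subject-effect variance held at the example value of 10 and the predictor read at zero, 15.0 points would be reported as 25.8. In the adjusted model, if the rule is carried over, 15.0 points would be read as 15.7 to 19.6 at mean covariates under the assumed SDs.

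The document does not support the stronger conclusion that the adjusted analysis will report a reference patient's risk, or that the primary conclusion would be reversed. The group coefficient and the direction of effect do not depend on the read-out. This is a low-cost improvement worth making before the analysis, not a flaw in the design.

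**What to change.** Add one sentence to the statistical methods: at each MCMC iteration, predict every randomised patient's risk under both arms, average over patients (and over the distribution of the subject effect, if that term is kept), and monitor the two averages and their difference. Report the posterior risk difference alongside the group coefficient for each model, without changing which model is primary.

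Averaging over all patients under both assignments is preferable to averaging each arm over its own patients, because the latter leaves chance covariate imbalance in the contrast.

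The cost is a few lines of R or OpenBUGS code. Design, data collection and sample size are unaffected.

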#### Methods for additional analyses (e.g. subgroup analyses) {20b}

Analyses will be performed in intention to treat. To verify the impact of possible deviations from the protocol, these analyses will be supplemented by an analysis per protocol. Subgroup analyses will be conducted according to the Glasgow Coma Scale on site (score either ≤ 8 or > 9).

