#### Methods in analysis to handle protocol non-adherence and any statistical methods to handle missing data {20c}

No statistical procedure for replacing missing values will be used. All variables and subjects will be considered in the descriptive analyses, but, for inference, 20% missing data or more will result in rejection of the variable or individual.

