### Study limitations

The incidence of moderate-to-severe hypoxaemia is the primary study endpoint. A 45% basal incidence of moderate-to-severe hypoxaemia may appear overstated to some experts, but it must be underlined that only severe trauma patients will be included and that a 45% incidence was reported in the last randomized PROMTT trial [13], in the era of damage-control resuscitation [54]. A 15% absolute reduction seems ambitious for a single intervention. However, previous studies using dornase alfa in animal lung injury models and in ventilated patients suffering atelectasis demonstrated striking results [35, 38–41, 55].

Because fluid loading regimens and transfusion strategies are based on local written protocols, they may act as potential confounding variables. However, this will be controlled by the stratification of the randomization at the centre level and adjustment of statistical analyses in cases of differences between groups.

In conclusion, this trial is the first multicentre, randomized controlled, double-blinded study adequately powered to test the hypothesis that aerosolized dornase alfa reduces the incidence of moderate-to-severe hypoxaemia in mechanically ventilated severe trauma patients.

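### The adjusted primary model takes all confounders together while replacement of missing values is barred, so it becomes a complete-case fit that falls short of intention to treat

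*Protocol article*

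**What the plan says.** Four statements in the protocol article bear on this.

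- **Model.** Statistical methods {20a} writes out a logistic model with an intercept, a group term and a subject effect. It then says: "This regression model without covariates except group will be completed for taking into account potential confounding variables". On how this is done: "In the model, the entire set of these variables will be added and, secondly, selected using stochastic search variable selection". The confounders are not listed and are not described as baseline variables.
- **Missing values.** Sections {20a} and {20c} both state: "No statistical procedure for replacing missing values will be used". No exception is made for covariates.
- **Rejection rule.** The same two sections add that "for inference, 20% missing data or more will result in rejection of the variable or individual". They do not say when the variable goes and when the individual goes, or over which variables an individual's percentage is counted.
- **Population.** Section {20b}: "Analyses will be performed in intention to treat", with a per-protocol analysis as a supplement.

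The Study limitations section names fluid loading and transfusion strategies as possible confounders. It relies on centre stratification and on "adjustment of statistical analyses in cases of differences between groups" to control them.

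**The concern.** A regression that holds all candidate covariates can use a patient only if every one of those covariates has a value or a distribution. With replacement barred, a patient with one gap must be left out, even when allocation and the primary outcome are recorded. The 20% rule does not prevent this. It removes variables and individuals at or above the limit, but gives no way of fitting a retained patient who has a gap below it.

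Two things are at stake. Outcome data already collected are left out of the adjusted result, which costs the precision that adjustment is meant to add. And the group-only and adjusted models are fitted to different patients, so their treatment effects are not directly comparable. The variable-selection step has the same problem, because all candidates must be in the model together.

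**Working it through.** **Can the statements hold together?** Take a randomised patient with known arm and outcome and one missing value in a covariate that the 20% rule keeps.

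1. The group-only model needs arm and outcome. The patient is in.
2. The full-covariate model needs every covariate. The linear predictor is undefined unless something stands in for the gap.
3. Supplying a value is ruled out by {20a} and {20c}. Supplying a distribution is arguably ruled out too, and {20a} specifies no distribution for any covariate.
4. The patient is therefore left out of the full-covariate and selection fits, and the adjusted set is smaller than the intention-to-treat set of {20b}.

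The 20% individual rule does not rescue this patient. If, for illustration, there were ten covariates and the percentage were counted over them, one gap is 1/10 = 10%. The rule nominally keeps the patient, but the model still cannot use the record.

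**Size.** The plan gives no figure for this loss, so there is none to reproduce. The total randomised is from Sample size {14}: 250 + 250 = 500. The number of covariates k and the missing fraction m of each are not in the document and are assumed below.

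*Case A: one incomplete covariate just under the plan's limit, m = 19%.*
- Lost: 0.19 × 500 = 95; left: 405.
- Standard-error factor from the smaller sample: 1/√0.81 = 1.11.
- For illustration only, take an unadjusted comparison of 0.45 with 0.30 (the rates in {14}), equal arms and two-sided 5% (assumed; the plan states no threshold). Power is 93.6% with 500 patients and 87.9% with 405.

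*Case B: k = 10, m = 3% each.* The loss depends on how far the gaps fall in the same patients.

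| Overlap of gaps | Share lost | Patients of 500 | Standard-error factor |
|---|---|---|---|
| Complete (same patients) | m = 3% | 15 | 1/√0.97 = 1.02 |
| Independent | 1 − (1 − m)^k = 1 − 0.97^10 = 26.3% | 131 | 1/√0.737 = 1.16 |
| None (all different patients) | k × m = 30% | 150 | 1/√0.70 = 1.20 |

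If missing data cluster in particular patients, the loss moves towards the first row. These figures leave out any loss of outcomes.

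**The case against.** **The text contains no complete-case rule.** This is true. A reader might infer that every patient missing one baseline covariate is excluded. The document does not say so: a patient whose only gap is in a variable rejected at 20% or more stays in, and the word baseline is not used for the confounders. What stands is narrower: a gap in a retained covariate cannot be fitted under the rules as written.

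**The primary analysis is untouched.** This largely stands. The group-only model is the one written out in full, and a missing covariate does not remove anyone from it. The standing of the adjusted model is itself unsettled, since the Study limitations section makes adjustment conditional on group differences. But that section also relies on adjustment to control local practice, so the adjusted result matters.

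**The loss may be close to nil.** This is possible. Centre and severe brain injury are stratification factors and the Injury Severity Score is an eligibility criterion, so these should be nearly complete. Structured data entry and monitoring point the same way.

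**Bias is not the issue.** If the covariates are measured before randomisation, their missingness cannot depend on treatment, and the complete cases still compare randomised arms. The cost is then precision and generalisability. A reader might also infer that adjustment and change of population cannot be told apart. They can, by refitting the group-only model on the same patients, though that does not bring the lost patients back.

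**A Bayesian model can treat a missing covariate as an unknown.** It can, and that is the remedy. The plan does not provide for it, and an unqualified ban on replacement reads against it.

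**This belongs in the statistical analysis plan.** The covariate list may well be there, and its absence here is no fault. The ban, however, is stated twice in the protocol and conflicts with the protocol's own analysis population.

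**Conclusion.** The point holds for the adjusted and variable-selection models only. With all confounders entered together and replacement barred, these become complete-case fits and fall short of the intention-to-treat set.

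The size cannot be read from the document. A single covariate at 19% missing would cost 95 of 500 patients while complying with the 20% rule. Ten covariates at an assumed 3% each would cost between 15 and 150. The figure of 131 needs independent gaps as well as the assumed k and m, and should not be quoted as an expected loss. Complete covariates would mean no loss.

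The documents do not support reading this as a failure of the trial's main comparison. The consequence is lost precision and two results on different patients. It should be corrected because the conflict lies in stated rules and the remedy is cheap.

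**What to change.** In {20a} and {20c}:

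1. Limit the no-replacement rule to outcomes.
2. Restrict the adjustment set to covariates measured before randomisation, and bring the conditional wording in Study limitations into line with {20a}.
3. Give each incomplete covariate a distribution within the OpenBUGS model already planned, or use a simple fill made blind to arm.
4. State that no randomised patient with a known primary outcome is rejected under the 20% individual rule because of missing covariates. Without this, item 3 would not achieve its purpose, since that rule would still remove such patients.

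The group-only, full-covariate and selection models then use the same patients, in line with {20b}. The cost is a few sentences and a few lines of model code, which can be settled while analysts are blinded. The downside is a distributional assumption for the incomplete covariates.
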